Specifically, fractional CO_2_ laser treatment has been reported as a new resurfacing technique in SD treatments [9]. Here, fractional CO_2_ forms micro-thermal zones of damage, the necrotic debris is expelled, and neo-collagenesis occurs [15]. This technique stimulates epidermal turnover and dermal collagen remodeling, which leads to important improvements in texture and appearance in many types of scars, such as stretch marks [16]—mainly in mature striae [2]. After treatment with fractional CO_2_ laser, full recovery with normal epidermis, parallel arrangement of the collagen bands, and perivascular aggregation of inflammatory cells were demonstrated [16]. In phototype IV skin, the use of CO_2_ laser treatment has been discouraged on account of the high risk of pigmentary alteration [17], although theoretically, this type of laser stimulates fibroblast activity and improves lesions through controlled skin abrasion [18]. Regarding adverse effects, there are a few, and some are self-limiting, such as post-inflammatory hyperpigmentation; however, these effects can be fixed naturally in a few months after treatment [2].

Additionally, CO_2_ laser treatment is more painful and requires a longer recovery time [19] when compared with non-ablative lasers. Studies have shown a significant decrease in the strial surface area after resurfacing with fractional CO_2_ laser treatment when compared with topical therapy (10% glycolic acid + 0.05% tretinoin) [20]. Lee et al. also demonstrated that fractional CO_2_ laser treatment, specifically at 10,600 nm, had a positive effect on late-stage SD, with clinical improvement with only one session [21]. When used in striae albae, fractional CO_2_ laser treatment was shown to be effective in subjects with skin types III and IV [20], and another study also demonstrated that two out of five patients with striae albae showed changes after 4-week treatment intervals with fractional CO_2_ laser [22].

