### 2.5. Intervention

Regarding the clinical procedures, the CO_2_ laser (CO_2_RE^®^, Candela, Marlborough, MA, USA) group will undergo three sessions, once a month over 3 months. The laser procedure has the following indications: laser tip diameter from 1 to 10 millimeters (mm), according to the width of the lesions; pulse power of 100 W; and repetition rate of 20 Hz using a single pass. During this procedure, a cryotherapy advice (Cryo 6, Zimmer, Germany) will be applied to reduce any pain. Since laser absorption is related to skin properties [28], there is a need to have both the reflectance and absorbance spectra of human skin. This is the key to quantitatively and non-invasively analyzing skin components. Figure 2 represents the relative penetration of different wavelength in all skin layers. Figure 3 represents a hyperspectral skin image, with the reflectance of different wavelength in the visible light range.

The FRF group will also undergo three sessions, once a month over 3 months. The procedure of this treatment will be performed with a set of 24 RF conductive needles. Each needle has a length of 2500 micrometers (μm). Patients will receive initial doses of 20–40 mJ/pin, and the doses will be increased at each session based on patient tolerance. All treated areas will receive a pass based on the treatment site and patient tolerance. During this procedure, cryotherapy will be applied with a Zimmer G system to reduce the patient’s pain.

For clinical improvement, before and after photos of an individual that went through laser CO_2_ treatment for abdominal striae will be used as a control (Figure 4); high-resolution digital photographs will be taken before and after both treatments at every session, starting at the baseline. Two physicians blinded to the study will compare these photographs using quartile scoring criteria for the assessment (0 = no improvement; 1 = mild (25% improvement); 2 = moderate (>25 ≤ 50% improvement); 3 = good (>50 ≤ 75% improvement); 4 = excellent (≥76% improvement)).

Additionally, measurements of cutaneous temperature, pH, and skin elasticity will be taken at the baseline and before and after each treatment. Cutaneous temperature will be measured by a thermograph (FLIR i7), positioned at 7 cm away from the abdomen area. The skin pH will be measured by pH bands. The skin elasticity will be measured by an elastometer.

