## 3. Results

### 3.1. Primary Outcome

The primary outcome measure will focus on the change in the quartile scoring criteria by comparing the digital photos taken before and after each treatment (fractional CO_2_ laser and FRF) for clinical improvements in the affected area (abdomen). This process will be assessed by two physicians blinded to the study. Figure 4 will be the control, being compared to the pictures taken during the study.

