### 3.4. Adverse Events

Adverse events will be monitored for each treatment during the trial. Any adverse events or reactions that are thought to be causally associated with the intervention, such as discomfort, mild pain, tissue erythema, tissue edema, irritation, and hyperpigmentation or hypopigmentation of the tissue, will be reported and managed. The measurement of cutaneous temperature before and after the treatments will help us monitor any sudden and significant changes regarding inflammatory processes. If the individual performs any additional physical therapy a day before or 3 days after the treatment, it will also increase the possibility of erythema and irritation since heat is being applied to the skin, so it is not advisable to perform exercise during this time.

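### The primary 0–4 photo score has no level for worsening, so participants who look worse are scored the same as participants who are unchanged

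*Protocol article*

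**What the plan says.** Section 2.5 (Intervention) has two blinded physicians compare photographs using "quartile scoring criteria for the assessment (0 = no improvement; 1 = mild (25% improvement" and further bands of improvement, ending at "4 = excellent (≥76% improvement". Every level above 0 is a degree of improvement, and there is no level below 0.

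Section 3.1 (Primary Outcome) makes this score the main endpoint: "The primary outcome measure will focus on the change in the quartile scoring criteria by comparing the digital photos taken before and after each treatment".

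The document mentions visible unwanted skin changes in two other places:

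- The Introduction says that in phototype IV skin "the use of CO_2_ laser treatment has been discouraged on account of the high risk of pigmentary alteration". It then says of adverse effects that "there are a few, and some are self-limiting, such as post-inflammatory hyperpigmentation", and that these can resolve naturally within a few months.
- Section 3.4 (Adverse Events) lists pigment change among the events to be monitored under each treatment: "hyperpigmentation or hypopigmentation of the tissue, will be reported and managed". That sentence covers events thought to be causally associated with the intervention. Table 1 schedules adverse effects at months 1, 2 and 3.

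The Introduction frames the hypotheses in both directions: either treatment may be superior in efficacy and safety. Section 2.3 has no exclusion by phototype, and the Discussion hopes to include different skin types.

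**The concern.** A comparison that may favour either arm needs an outcome that can move both ways. This one cannot. A participant whose striae or surrounding skin look worse overall has only one level available, and it is shared with participants who are unchanged. The scale is stated and closed, so this is not a detail left to an analysis plan. Once the raters have recorded 0, no later analysis can separate the two groups.

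Worsening is a realistic possibility here. The protocol itself names a pigmentary risk with CO2 laser in one phototype and does not exclude that phototype. The last photographs are taken at month 3, while the Introduction allows a few months for pigment change to resolve.

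At stake is the between-arm difference on the primary outcome. If the arms differ in how often participants look worse, that part of the treatment difference is removed from the score.

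**Working it through.** **Plan's own figure.** There is none to reproduce. The protocol gives no rate of worsening, no standard deviation (SD) for the score and no target difference. The calculations below are illustrations on assumed values.

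**Inputs from the document.** 30 participants per arm (Section 2.2); scale 0 to 4 with no negative level (Section 2.5); significance at p < 0.05 (Section 3.5), taken here as two-sided.

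**Assumed inputs.** w = share of an arm that looks worse overall; k = points below 0 that such a participant would receive on a signed scale, taken as equal in the two arms; SD of the score 0.8, 1.0 or 1.2.

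**Step 1: size of the distortion.** A worsened participant who would score −k is recorded as 0, so the arm mean is raised by k × w. The difference CO2 minus FRF is therefore shifted by

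shift = k × (w_CO2 − w_FRF).

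| w_CO2 | w_FRF | Number worse of 30 (CO2, FRF) | Shift, k = 1 | Shift, k = 2 |
|---|---|---|---|---|
| 5% | 0% | 1.5, 0 | 0.05 | 0.10 |
| 10% | 0% | 3, 0 | 0.10 | 0.20 |
| 20% | 0% | 6, 0 | 0.20 | 0.40 |
| 30% | 0% | 9, 0 | 0.30 | 0.60 |
| 20% | 5% | 6, 1.5 | 0.15 | 0.30 |
| 30% | 10% | 9, 3 | 0.20 | 0.40 |
| 10% | 10% | 3, 3 | 0 | 0 |

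Swapping the arms reverses the sign. Since k is at least 1, the shift is at least 1 point times the difference in rates.

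**Step 2: a yardstick.** The difference detectable with 80% power is SD × (1.960 + 0.842) × √(2/30) = 0.723 × SD, which is 0.58, 0.72 or 0.87 points for SD 0.8, 1.0 or 1.2. At SD 1.0 and k = 1, the one-arm range of 0.05 to 0.30 is 0.05/0.723 = 7% to 0.30/0.723 = 41% of that difference.

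**Step 3: a worked example.** Suppose 24 in each arm score 2, the other 6 on CO2 look worse, and the other 6 on FRF are unchanged.

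- Current scale: both means are (24×2 + 6×0)/30 = 1.6, so the difference is 0.
- Signed scale: CO2 (24×2 − 6×1)/30 = 1.4 and FRF 1.6, so the difference is −0.2.
- Test on the signed scores: Welch p ≈ 0.46, Mann-Whitney p ≈ 0.71.
- Proportion worse, 6/30 against 0/30: Fisher p ≈ 0.024.

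In this example the signed mean recovers the lost 0.2 points but is not significant. The proportion worse is the more sensitive summary, which is why the fix asks for both.

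**The case against.** The strongest reply is that efficacy and safety are measured separately. The photo score is meant to grade improvement. Pigment change is a named adverse event, monitored under each treatment and scheduled at months 1 to 3, and in the worked example a complete adverse-event record would show the 6/30 against 0/30 contrast without any change to the score. This stands in part. A reader might infer that the scale hides harm from the trial as a whole, and the documents do not support that. But the adverse-event record is limited to events thought to be causally associated and does not enter the efficacy comparison. It does not replace a worse category in the blinded rating.

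Three other stronger readings also fail:

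- *The scale favours the CO2 arm.* The high pigmentary risk is stated for phototype IV only, adverse effects are described as few and partly self-limiting, and Section 3.4 lists pigment change without assigning it to one arm. No rates are given. A hyperpigmented participant whose striae improve may still score 1 to 4.
- *Raters must know which photograph is later.* They need not. Pairs can be shown in random order and decoded afterwards, even with a 0–4 scale. The article does not state the display order, a detail that a condensed article may leave to the full protocol.
- *Rating error can only push scores up.* That is so only at a true 0. A true 3 can be rated lower, and a true 4 can only be rated lower.

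Finally, an improvement-only quartile scale keeps comparability with studies that used it. This is a fair point, but the 0–4 score can be recovered from a signed one.

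**Conclusion.** The point holds as a limited but real weakness of the primary outcome. As defined in Sections 2.5 and 3.1, the score cannot tell worse from unchanged, so worsening is lost from the blinded efficacy comparison and can surface only through causally attributed adverse events.

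If worsening rates differ between arms, the mean difference is distorted by at least 1 point times the difference in rates, assuming that worsened participants lose the same number of points in each arm. The illustrative 0.05 to 0.30 points rests on assumed worsening of 5% to 30% in one arm only and a single level below zero. The documents support neither a size nor a direction, and the distortion is zero if rates are equal. The change is worth making because the lost information cannot be recovered once rating is done.

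**What to change.** Before any photographs are rated:

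1. Add at least one level below zero to the score in Section 2.5, with −1 defined as worse than baseline.
2. Show the two physicians each pair without dates and in random order. They state which image looks better and by which band; the sign is added afterwards from the key.
3. In Section 3.1, compare the arms on the signed score and report the proportion scored worse in each arm.
4. Also report the 0–4 score with negatives set to 0, for comparability with studies that used that scale.

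The cost is small: a rewording of the scale and a coded display order, with the same photographs, raters and visits. The downside is a slight departure from the usual quartile scale, which item 4 largely offsets.

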### 3.2. Secondary Outcome

Secondary outcome measures will focus on data changes regarding cutaneous temperature and skin pH and elasticity, assessed after the stria treatments (fractional CO_2_ laser versus FRF). Cutaneous temperature will be measured by a thermograph (FLIR E1), which will help to evaluate any inflammatory process; skin pH will be measured by pH bands; and skin elasticity will be measured by an elastometer.

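### Skin pH, a secondary outcome compared between arms, is read from pH bands of unstated step with no masking described, so readings are blurred by rounding and open to observer bias

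*Protocol article*

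**What the plan says.** Section 2.5 (Intervention) names the tool: "The skin pH will be measured by pH bands". Section 3.2 (Secondary Outcome) repeats it: "skin pH will be measured by pH bands; and skin elasticity will be measured by an elastometer". Neither place gives a step width, a range, a reading procedure or the person who reads the band.

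Section 3.2 sets the role of the measurement: "Secondary outcome measures will focus on data changes regarding cutaneous temperature and skin pH and elasticity, assessed after the stria treatments", with CO2 laser set against fractional radiofrequency. On timing, section 2.5 says that "measurements of cutaneous temperature, pH, and skin elasticity will be taken at the baseline and before and after each treatment".

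Masking appears twice, both times for photographs. Section 2.5 has "Two physicians blinded to the study will compare these photographs using quartile scoring criteria for the assessment". Section 3.1 (Primary Outcome) says of the photograph scoring: "This process will be assessed by two physicians blinded to the study". Nothing comparable is said for pH, temperature or elasticity.

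The arms look different at the session. One uses a CO2 laser; for the other, "The procedure of this treatment will be performed with a set of 24 RF conductive needles".

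**The concern.** Two separate weaknesses follow from choosing a band.

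- **Resolution.** If a band is matched to a printed colour key, the recorded value is rounded to the step of that key. The outcome is a change, so the rounding enters twice, once at each reading. An analysis plan cannot recover resolution that was never recorded.
- **Observer bias.** A colour match is a judgement. It is made immediately before and after a procedure whose type is evident to anyone present, and no masking of the reader is described. A small tendency to read one arm higher would appear as a treatment effect.

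At stake is the pH part of the secondary comparison. A real difference is harder to detect, and an apparent one is harder to trust. Temperature and elasticity are assigned devices (a thermograph and an elastometer), so pH is the only one of the three that depends on matching a colour.

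**Working it through.** The article gives no power, effect size, SD or pH step for this outcome, so there is no stated figure to reproduce.

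**Inputs from the article.** 30 per arm (section 2.2); significance at p < 0.05 (section 3.5), taken as two-sided; outcome analysed as change (section 3.2).

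**Assumptions.** SD of change 0.3 to 0.7 pH unit; band step w of 0.1 to 1.0; reading shift b of 0.1 or 0.2 in one arm.

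**Step 1: difference detectable with exact readings at 80% power.**

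δ = (1.960 + 0.842) × SD × √(2/30) = 2.802 × 0.2582 × SD = 0.723 SD

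This is 0.22 pH unit at SD 0.3, 0.36 at SD 0.5 and 0.51 at SD 0.7.

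**Step 2: effect of rounding on power.** Rounding one reading to step w adds a variance of about w²/12. A change uses two readings, so it adds about w²/6. For the same δ:

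Power = Φ(2.802 × √[SD² / (SD² + w²/6)] − 1.960)

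Example, SD 0.3 and w = 0.5: SD² = 0.0900 and w²/6 = 0.0417, total 0.1317. √(0.0900/0.1317) = 0.827. Then 2.802 × 0.827 − 1.960 = 0.357, and Φ(0.357) = 0.64.

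| SD of change | step 0.1 | step 0.3 | step 0.5 | step 1.0 |
|---|---|---|---|---|
| 0.3 | 79% | 74% | 64% | 38% |
| 0.4 | 80% | 76% | 70% | 50% |
| 0.5 | 80% | 78% | 74% | 58% |
| 0.7 | 80% | 79% | 77% | 68% |

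Simulation agrees to within about one point, except at SD 0.3 with step 1.0, where it gives 39 to 40% rather than 38%. It used baseline pH with mean 5.5 and SD 0.5, both readings rounded, a t test on change and a true difference of 0.736 SD.

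If only one rounded value per patient were analysed, the added variance would be w²/12 and the loss smaller: at SD 0.3, power of 71% at step 0.5 and 52% at step 1.0. Section 3.2 speaks of changes, so the two-reading figures are the relevant ones.

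The loss comes from added noise. The difference in means is nearly preserved: for single readings with SD 0.5, even at step 1.0, the rounded difference is 0.99 to 1.01 times the true one.

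**Step 3: effect of a reading shift in one arm when there is no true difference.** With SE = SD × √(2/30):

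False-positive rate = Φ(b/SE − 1.960) + Φ(−b/SE − 1.960)

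Example, SD 0.3 and b = 0.2: SE = 0.0775 and b/SE = 2.582, which gives 73%.

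| SD of change | b = 0.1 | b = 0.2 |
|---|---|---|
| 0.3 | 25% | 73% |
| 0.5 | 12% | 34% |
| 0.7 | 9% | 20% |

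The nominal rate is 5%. Replacing SD² by SD² + w²/6 at step 0.5 lowers the b = 0.2 column to about 57%, 30% and 19%, so rounding offers little protection against bias.

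**The case against.** **Small differences are not shown to be lost.** A reader might infer that any difference smaller than one colour step disappears. The figures do not support that. At SD 0.3 the difference studied is 0.22 unit, below a 0.3 step, yet power falls only from 80% to 74%. Differences are blurred, and the loss is large only for coarse bands set against a small SD. This objection stands.

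**The size depends on figures the article does not give.** With steps of 0.1 to 0.3 the loss is between nothing and about 6 points; with a step of 1.0 and SD 0.3 it is about 40. Nothing in the article rules out narrow-range bands, and the full protocol may specify them. It also does not say how the bands are read, so matching by eye is an assumption. This stands and limits confidence. It does not remove the point, because the band is the stated instrument in two sections.

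**Knowledge of the arm is inferred.** A reader might take it as established that staff know the arm when they read the band. The article does not say who reads it. The inference is reasonable once treatment has begun. It may not hold at baseline: Table 1 appears to place randomisation at the same visit as the baseline measures, and their order is not given.

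**Missing masking is not peculiar to pH.** Temperature and elasticity are taken at the same sessions with no masking described. That is true. What sets pH apart is that the value itself is a colour judgement, which makes it easier to shift.

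**The stake is small.** No power claim or specific hypothesis is attached to pH, and the Discussion gives the secondary measures a largely descriptive purpose. This stands and is reflected in the grading.

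**Conclusion.** The concern holds in a limited form. The article assigns to a between-arm secondary outcome an instrument whose step is unstated and whose reading is, on the natural understanding of a pH band, a visual judgement with no masking described.

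For an assumed SD of change of 0.3 to 0.7, rounding reduces 80% power to about 74 to 79% at step 0.3, 64 to 77% at step 0.5 and 39 to 68% at step 1.0. Observer bias is potentially the larger problem: an assumed shift of only 0.1 to 0.2 unit in one arm takes the false-positive rate from 5% to between 9% and 73%. Whether such a shift would occur cannot be told from the article.

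A reader might infer that the trial's main result is compromised. It is not: the primary outcome is the photograph score, which has its own blinded readers and does not use pH. This is a minor, low-cost improvement rather than a flaw that threatens the trial.

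**What to change.** In sections 2.5 and 3.2, replace the pH bands with a flat-surface skin pH meter that has a numeric display and a resolution of at least 0.1 unit. Use the same unit in both arms and at all visits.

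At 0.1-unit resolution, power stays at 79 to 80% across the assumed SDs, and the colour judgement is removed. The operator may still know the arm, so pH would then be in the same position as temperature and elasticity.

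The cost is one handheld meter and its calibration. No visit, staff member or patient is added.

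Keeping narrow-step bands and having coded photographs of them read by the two blinded physicians would also work, but it is more laborious than it looks. One baseline reading plus two at each of three sessions is 7 per person, so 7 × 60 = 420 band photographs at most, each read twice. The meter is the simpler choice.

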## 3. Results

### 3.1. Primary Outcome

The primary outcome measure will focus on the change in the quartile scoring criteria by comparing the digital photos taken before and after each treatment (fractional CO_2_ laser and FRF) for clinical improvements in the affected area (abdomen). This process will be assessed by two physicians blinded to the study. Figure 4 will be the control, being compared to the pictures taken during the study.

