### 3.5. Data Collection and Statistical Analysis

Data collection will be performed in every session for each treatment. The data from this study will be analyzed using the Statistical Package for the Social Sciences (SPSS) V.21 software. A *p*-value < 0.05 will be considered statistically significant. Measured data will be expressed as mean ± SD.

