**Figure 4 healthcare-10-02372-f004:**
[figure not shown]
Before (**A**) and after (**B**) control photos of abdominal striae of an individual subjected to laser CO_2_ treatment.

**Table 1 healthcare-10-02372-t001:** Timing of visits and data collection, according to the Standard Protocol Items: Recommendations for Interventional Trials (SPIRIT).

				Treatment Period		
		Screening	Baseline 0-Month	1-Month	2-Month	3-Month
Patient	Eligibility Informed consent Clinical data Physical examination Randomization	X	X X X X			
Intervention	Fractional CO_2_ laser: Group A			1 session per month for 3 months		
	Fractional radiofrequency: Group B			1 session per month for 3 months		
Outcomes	Digital photo collection		X	X	X	X
	Cutaneous temperature		X	X	X	X
	Skin pH		X	X	X	X
	Skin elasticity		X	X	X	X
Participant Safety	Adverse effects			X	X	X

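### The primary photo score has no single decisive comparison and does not exclude images taken just after a procedure, so it can record acute skin reaction instead of improvement

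*Protocol article*

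**What the plan says.** Section 3.1 sets the primary outcome as the "change in the quartile scoring criteria by comparing the digital photos taken before and after each treatment", with the two modalities named in parentheses. Section 2.5 gives the timing: "high-resolution digital photographs will be taken before and after both treatments at every session, starting at the baseline". It then says who scores them: "Two physicians blinded to the study will compare these photographs using quartile scoring criteria for the assessment". The scale has five ordered grades, from 0 for no improvement to 4 for excellent improvement.

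The laser "group will undergo three sessions, once a month over 3 months"; for the other arm, "The FRF group will also undergo three sessions, once a month over 3 months". In Table 1 the row "Digital photo collection" is marked at baseline and at months 1, 2 and 3. The sessions lie inside the 1- to 3-month treatment period, and no visit follows it.

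Section 3.4 lists reactions expected from the intervention, among them "discomfort, mild pain, tissue erythema, tissue edema, irritation". The only testing rule, in section 3.5, is a p-value below 0.05.

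**The concern.** A primary endpoint should fix which two images are compared, and when, before any image is scored. Here the photographs handed to the raters include some taken immediately after an ablative laser pass or a 24-needle radiofrequency pass. The Introduction describes the intended benefit as a later process: thermal injury, then formation of new collagen. A same-day image cannot show that. It can show redness and swelling.

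Three consequences follow. The score may measure acute reaction. Acute worsening cannot be recorded, because the scale stops at 0. And with three sessions and no named primary one, the choice among several results is left open. Raters may also be able to tell the arms apart from fresh device marks. None of this can be repaired after data collection if no suitable final image exists.

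**Working it through.** **1. Which image pairs does the text allow?** Take the sessions at months 1, 2 and 3, as Table 1 is laid out, with one before and one after image at each. That gives 3 × 2 = 6 session images plus the baseline image, 7 per participant. Three families of comparison fit the wording:

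| Pair scored | Number | Later image taken just after a procedure? |
|---|---|---|
| Before vs after within one session | 3 | Yes |
| Baseline vs after image of each session | 3 | Yes |
| Baseline vs before image of each session | 3 | No |

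Two of the three families score a fresh post-procedure image. No section rules them out.

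**2. What would such an image show?** Section 3.4 names erythema, edema and irritation. Sections 2.5 and 3.4 also use this same before-and-after window for skin temperature, in order to detect inflammation. The protocol thus treats the window as one in which inflammation appears, and uses it for efficacy too.

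**3. What can the scale record?** Its minimum is 0, no improvement. A participant whose skin looks worse and one whose skin looks unchanged both score 0. The score is itself a graded percentage improvement between two images, so there is no baseline score from which to take a change.

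**4. Error rate, conditional on testing every session.** The plan's own figure is 0.05, and one comparison gives 0.05. For k = 3 independent comparisons:

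1 − (1 − 0.05)³ = 1 − 0.8574 = 0.1426.

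Session scores in the same people are correlated, and the document gives no correlation, so it is assumed. Simulating three equicorrelated two-sided z-tests (1,000,000 draws) gives:

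| Assumed correlation | P(at least one p < 0.05) |
|---|---|
| 0 | 0.143 |
| 0.5 | 0.126 |
| 0.7 | 0.109 |
| 0.9 | 0.084 |

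Over correlations from 0 to 0.7 this is about 11–14%.

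**5. Cost of keeping all three primary.** Bonferroni would need 0.05/3 = 0.0167 per test. With 30 per arm and 80% power (normal approximation), the detectable standardized difference is (z for 1 − α/2, plus 0.842) × √(2/30):

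- single test at 0.05: (1.960 + 0.842) × 0.258 = 0.72;
- three tests at 0.0167: (2.394 + 0.842) × 0.258 = 0.84.

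The protocol states no power, effect size or SD, so these figures are only context and contradict nothing in it.

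**The case against.** The strongest defence is that treatment in section 3.1 means the modality, since the parenthesis names the two modalities and the Discussion likewise refers to the respective treatments. Table 1 shows one photo entry per visit. On that reading raters compare baseline with follow-up, and no passage says that a same-day pair is the scored contrast. This has force: the document does not prove that acute reaction will be scored. It leaves the pair ambiguous, though, and does not rescue the endpoint. Section 2.5 still schedules an after image at every session, hands those same photographs to the raters and excludes none. Table 1 shows no later visit at which a healed image would be taken.

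Four stronger readings are tempting and are not supported:

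- **That the false-positive rate exceeds 5%.** Nothing says that each session, or each rater, will be tested separately. Six tests would give 0.265 if independent and 0.164 at correlation 0.7, but an analysis plan not shown here may name a single test.
- **That the raters will be unblinded.** A laser tip of 1 to 10 mm and a 24-needle array may leave different marks, but no such marks are described. This is a risk only.
- **That an ordinal score is wrongly summarised by a mean.** "Measured data will be expressed as mean ± SD" may refer only to temperature, pH and elasticity, for which the article uses the word measured. The choice of test or model belongs to the analysis plan.
- **That the primary result will be reaction instead of improvement.** Neither the size of this distortion nor its direction between the arms can be derived from the document.

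**Conclusion.** The point holds as a defect in how the primary endpoint is defined. Followed as written, sections 2.5 and 3.1 permit scoring of images taken just after a procedure, name no decisive comparison, and use a scale that cannot register worsening. The reference to a change in an improvement score is undefined on its face.

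The resulting bias cannot be quantified. The 11–14% family-wise error rests on two assumptions: that all three sessions are tested between arms at 0.05, and that the correlation lies between 0 and 0.7. It supports naming one time point but is not the main ground for the finding. Possible unblinding is an added risk.

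The timing argument relies on Table 1 as laid out. If the last session in fact precedes month 3, a photograph free of same-day reaction already exists at that visit, and the text need only say that it is the one scored.

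**What to change.** Define one primary comparison in section 3.1: the quartile improvement score of the baseline pre-treatment photograph against one named final photograph that does not follow a procedure on the same day, scored on de-identified images. Drop the reference to a change in the score. Make session-level scores secondary, and keep same-day post-session photographs for safety documentation only.

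The month-3 photograph taken before that day's session is already in the schedule, so using it costs only a change of wording. If the third session is at month 3, this image omits that session's effect. Capturing it would require one later photograph, and so an assessment that Table 1 does not now contain. Session-level scores also lose their primary status. In return, one named comparison tested once keeps the type I error at the stated 0.05.
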